### Endpoints

2.7

The primary efficacy endpoint of the OPTIMA‐4 trial is a composite of cardiovascular death, myocardial infarction, unplanned revascularization, ischemic stroke, and systematic thromboembolism during 12‐month follow‐up. The primary safety endpoint is major bleeding and clinically relevant nonmajor bleeding (CRNMB) defined by the International Society of Thrombosis and Hemostasis (ISTH) during 12‐month follow‐up.^20^ The composite secondary endpoint of net adverse events included all‐cause death (cardiovascular death, noncardiovascular death), acute myocardial infarction (fatal or nonfatal, Q‐wave or non‐Q‐wave), systemic thromboembolism, unplanned revascularization (target or nontarget vessel, target or nontarget lesion), stent thrombosis (possible, probable, definite), stroke (hemorrhage or ischemic) and bleeding (ISTH or Bleeding Academic Research Consortium [BARC] criteria) during 12‐month follow‐up.^20^, ^21^

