### Sample size determination and statistical analysis

2.9

The OPTIMA‐4 trial aims to simultaneously test the following two hypotheses of dabigatran‐based DATT in eligible patients: (1) clopidogrel is superior to ticagrelor regarding major bleeding and CRNMB events and (2) clopidogrel is noninferior to ticagrelor regarding the composite efficacy endpoint. According to the RE‐DUAL PCI trial, the anticipated incidence of annual efficacy endpoint is 18.9% in the arm of ticagrelor.^9^ We set a noninferiority margin ratio of 1.38 and *α* of .025 (one‐sided), 655 patients in each group are required to achieve a statistical power of 80%.^9^ Assuming that 11% of patients will be lost to follow‐up (1%) or drop‐out (10%), at least 736 patients are finally required for each randomized group. Then, the final sample size is estimated to be 1472. With this sample size, the anticipated power for the composite safety endpoints (14.5% and 21.2% in clopidogrel and ticagrelor groups, respectively) would be around 87.1%.^9^

Descriptive statistics will be used to summarize and analyze the baseline demographic characteristics (mean, SD, median, minimum, first quartile, third quartile, and maximum for continuous measures; frequency counts and percentages for categorical measures) of each treatment group; the Student *t* test or analysis of variance will be used for the comparison of continuous variables and *χ*
^2^ test for the comparison of categorical variables across treatment groups.

To control the type I error at one‐side 0.025 level, a hierarchical procedure for multiple testing will be used. The paradigm of the hierarchical procedure in OPTIMA‐4 trial is detailed below:
Step 1:Superiority of dabigatran combined with clopidogrel to dabigatran combined with ticagrelor concerning major bleeding and CRNMB is met at the one‐sided 0.025 level of significance.Step 2:Noninferiority of dabigatran combined with clopidogrel to dabigatran combined with ticagrelor for the efficacy endpoint is met at the one‐sided 0.025 level of significance.

If step 1 fails to meet statistical significance, step 2 will not be performed.

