The primary endpoints will be treated as time‐to‐event endpoints, and the Kaplan–Meier method will be employed to estimate the cumulative incidences of endpoints by treatment group. The primary endpoints between the two groups will be compared using the Cox proportional hazards model with treatment as a fixed effect and adjusted for other covariates separately. The estimated hazard ratio (HR) and two‐sided 95% confidential interval (CI) or one‐sided 97.5% CI for the noninferiority test will be provided. For the noninferiority test in the composite efficacy endpoint, the noninferiority margin is 1.38 on the HR scale. The upper boundary of CI for the HR (one‐sided 97.5%) will be compared to this margin. All the above analyses will also be conducted in predefined subgroups. The secondary time‐to‐event endpoints will be analyzed using the methods mentioned above. All statistical analyses will be performed using SAS version 9.4 (SAS Institute Inc.).

The analysis sets are as follows: (1) full analysis set (FAS): according to the intention‐to‐treat principle, the FAS is defined as all patients being randomized who receive at least one dose of the assigned treatment; (2) per‐protocol analysis set (PPS): the PPS is a subset of FAS, which includes all randomized patients meeting the study eligibility criteria, without major protocol deviation (see Supporting Information: Appendix 5),^21^, ^24^ without using drugs or receiving treatments that may interfere with the evaluation of efficacy, and accomplishing all efficacy assessments after randomization; and (3) safety set (SS): the SS includes all randomized patients with at least one safety assessment after randomization. The analysis of primary endpoints will be performed on both FAS and PPS, with FAS analysis as the primary analysis. Consistency of the results on primary endpoints between FAS and PPS will demonstrate the robustness of the conclusion. Safety analyses will be performed on the SS.

Subgroup analyses are planned across major subgroups by age, sex, body mass index, diabetes, ACS diagnosis, the Synergy between Percutaneous Coronary Intervention with Taxus and Cardiac Surgery (SYNTAX) score, and CHA_2_DS_2_‐VASc score (see Supporting Information: Appendix 6).

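### The per-protocol set drops patients who die before month 12, so its agreement with the full analysis set cannot by itself demonstrate robustness

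*Protocol article*

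**What the plan says.** The Endpoints section defines the primary efficacy endpoint as "a composite of cardiovascular death, myocardial infarction, unplanned revascularization, ischemic stroke, and systematic thromboembolism" over 12 months. The section on study visits schedules efficacy follow-up to month 12, with clinic visits at 1, 6 and 12 months and telephone contacts in between.

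The section on sample size and statistical analysis opens its account of the primary analysis with "The primary endpoints will be treated as time"-to-event endpoints, to be compared by a Cox model. It then defines the analysis sets. The PPS is a subset of the FAS. Its members must be eligible, have no major deviation (Appendix 5 is cited for this item), qualify as "without using drugs or receiving treatments that may interfere with the evaluation of efficacy", and finally meet the condition "and accomplishing all efficacy assessments after randomization". No exception is stated for death or for a patient who has already had an endpoint event.

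The primary endpoints are analysed in both sets, "with FAS analysis as the primary analysis". The role of the PPS is then stated: "Consistency of the results on primary endpoints between FAS and PPS will demonstrate the robustness of the conclusion".

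**The concern.** A patient who dies in month 4 has not completed the 6- and 12-month assessments. The completion condition therefore removes that patient, the death itself, and any infarction or stroke recorded before it. Yet a cardiovascular death is one of the events that the efficacy analysis exists to count. The Endpoints section also classes deaths of unknown cause as cardiovascular, which adds to the events at risk of removal.

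The interfering-treatment condition has a related weakness. It carries no time limit, so treatment given in response to an endpoint event could disqualify the patient who had the event. Allocation is open-label, so such treatment could differ between arms.

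Both conditions make membership depend on what happens after randomization, including the outcome. A time-to-event analysis does not need a completion rule, because incomplete follow-up is censored and death is an event. At stake is the robustness sentence: a set selected partly on survival cannot check a conclusion about a composite that contains death.

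**Working it through.** **The plan's own figures.** Inputs from the sample-size section: ticagrelor event rate 18.9%, margin ratio 1.38, one-sided alpha 0.025, power 80%. A Farrington–Manning score test for the risk ratio, with equal true rates, gives 654.4, so 655 per arm. Allowing for 11% losses, 655 / 0.89 = 736 per arm. Both match the article, and neither is in dispute.

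**Events removed.** Expected primary events per 655 patients: 0.189 × 655 = 123.8, about 124. The documents give no cardiovascular mortality; assume 3% to 5% over 12 months.

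- 0.03 × 655 = 19.7, about 20 events; 0.03 / 0.189 = 16%.
- 0.05 × 655 = 32.8, about 33 events; 0.05 / 0.189 = 26%.

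**Loss of information, arms equal.** Let d be the cardiovascular mortality, n = 655(1 − d) the patients left, and q = (0.189 − d)/(1 − d) their event rate. On the log risk ratio scale, SE = √[2(1 − q)/(qn)] and power = Φ(ln 1.38 / SE − 1.96).

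| d | n | q | SE | power |
|---|---|---|---|---|
| 0 | 655 | 0.189 | 0.1145 | 80% |
| 3% | 635 | 0.164 | 0.1267 | 72% |
| 5% | 622 | 0.146 | 0.1369 | 65% |

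This ignores the other PPS exclusions.

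**Effect on the hazard ratio if only cardiovascular death differs.** The Introduction reports that ticagrelor lowered cardiovascular death by 21.6% against clopidogrel, both with aspirin. Take 4.0% cardiovascular death on ticagrelor (assumption), so 4.0 / (1 − 0.216) = 5.1% on clopidogrel. Let 14.9% have a nonfatal event in both arms.

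- Ticagrelor composite: 1 − 0.851 × 0.960 = 18.3%.
- Clopidogrel composite: 1 − 0.851 × 0.949 = 19.2%.
- FAS: HR = ln(1 − 0.1924) / ln(1 − 0.1830) = 1.057.
- PPS with deaths removed: 14.9% in both arms, HR = 1.00.

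This treats fatal and nonfatal events as independent. If no patient has both, the composites are 18.9% and 20.0%, giving an FAS HR of 1.065. The PPS rates are 14.9/96.0 = 15.5% and 14.9/94.9 = 15.7%, giving a PPS HR of 1.01. The picture is the same.

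**The direction is not fixed.** Keep 4.0% fatal and 14.9% nonfatal on ticagrelor, mutually exclusive, and suppose a ratio of 1.2 (assumption).

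- Applied to nonfatal events only, clopidogrel has 17.9% + 4.0% = 21.9%. The FAS HR is 1.18 and the PPS HR is 1.22, so the PPS moves away from 1.
- Applied to both components, the FAS and PPS HRs are both about 1.23, so almost nothing changes.

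**Extreme case.** Suppose clopidogrel is truly at a risk ratio of 1.38, the whole excess is fatal, and 10% to 40% of ticagrelor events are fatal (all assumptions). In simulation with 655 per arm, the analysis that keeps deaths declares noninferiority in 2.5% to 2.7% of trials. With deaths removed, the median ratio is about 1.08 and noninferiority is declared in 53% of trials at a 10% fatal share, falling to 36% at 40%. This marks the outer limit and is not an expectation.

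**The case against.** The strongest reply is that the authors probably meant all assessments that were due. The same section says that the primary endpoints, death included, will be analysed in the PPS as times to event, and a blinded committee adjudicates every one of them. On that reading an adjudicated death is a completed assessment. This may well be the intention, but the text does not say it. Appendix 5, which is not shown, is cited for major deviations and not for the completion condition. A programmer who applied the stated rule would build the wrong set.

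Several limits do stand. The noninferiority decision rests on the FAS, which does not remove patients for dying during follow-up. Patients with nonfatal events who complete follow-up stay in the PPS, so it is selected but still informative. No list of interfering treatments is shown, so how often that condition would act on patients after an event is unknown.

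A reader might infer that both sets are biased toward no difference and could agree on a false claim, because non-adherence dilutes the FAS while lost deaths pull the PPS toward 1. The documents do not support this as a general statement. The pull toward 1 arises only if the excess is concentrated in deaths, and the article anticipates 10% drop-out, not patients switching to the other drug. Any figure for dilution would rest on a crossover rate that the documents do not give.

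**Conclusion.** The point holds as a defect in a stated rule. As written, PPS membership depends on survival to month 12 and possibly on treatment after an event, so agreement between FAS and PPS cannot by itself demonstrate robustness. Under an assumed 3% to 5% cardiovascular mortality, the PPS would lose 16% to 26% of its expected primary events. With the cited 21.6% difference confined to cardiovascular death, it would show an HR of about 1.00 where the FAS shows about 1.06. That shift is small against a margin of 1.38. Larger distortions need an excess concentrated in deaths, and the documents give neither the mortality nor its split between arms.

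It would go too far to conclude that the noninferiority test is compromised: the primary FAS comparison is untouched. This should be fixed, but it does not threaten the trial's main result.

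**What to change.** Make three wording changes in the PPS definition, before database lock so that nobody decides with the data in view who counts as complete:

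1. Delete the completion condition, or state that death or a first primary event counts as complete follow-up.
2. Apply the interfering-treatment and deviation exclusions only to deviations that precede any primary event.
3. Keep patients with later deviations or loss to follow-up in the set, censored at that point, with all earlier primary events counted.

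The cost is a little extra programming; no new data or patients are needed. Censoring at a deviation may itself be informative: the Discussion notes that bleeding can lead to stopping treatment and so to more ischemic risk. The PPS should therefore remain supportive, and the robustness sentence should be softened to match. Requiring the upper limit to fall below 1.38 in both sets would be a new decision rule with its own power cost, and this repair does not need it.

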### Study visits and follow‐up

2.8

All subjects will be followed up at 1 month (±7 days), 6 months (±7 days), and 12 months (±7 days) in the outpatient clinic, and at 2 weeks (±7 days), 2 months (±7 days), and 3 months (±7 days) by telephone. The patients' primary and secondary endpoints, (severe) adverse events, medications, and the results of the tests mentioned above will be carefully recorded during the follow‐up.

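### Read literally, the per-protocol completeness condition drops adherent patients who die before month 12, so the supportive PPS analysis is selected on cardiovascular death

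*Protocol article*

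**What the plan says.** All references are to the protocol article.

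- **Section 2.9 (analysis sets).** The PPS is a subset of the FAS. Besides eligibility, no major deviation and no interfering treatment, it requires "accomplishing all efficacy assessments after randomization". No exception is written for death or for a patient who already has an endpoint.
- **Section 2.8.** The last scheduled assessment is at "12 months (±7 days) in the outpatient clinic".
- **Section 2.7.** The primary efficacy endpoint "is a composite of cardiovascular death, myocardial infarction, unplanned revascularization, ischemic stroke" and systemic thromboembolism, over 12 months.
- **Section 2.9 (analysis).** "The primary endpoints will be treated as time‐to‐event endpoints", with Kaplan–Meier estimates and a Cox model; for efficacy, "the noninferiority margin is 1.38 on the HR scale".
- **Section 2.9 (use of the sets).** Primary endpoints are analysed on both sets, "with FAS analysis as the primary analysis". The plan adds: "Consistency of the results on primary endpoints between FAS and PPS will demonstrate the robustness of the conclusion".

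The FAS is defined by randomisation and at least one dose. It carries no completeness condition.

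**The concern.** A patient who takes the assigned drugs exactly as planned and dies at month 3 cannot attend the month-6 or month-12 visit. Applied as written, the condition puts that patient outside the PPS, along with any infarction or stroke recorded before the death. Membership would then depend on something that happens after randomisation and is itself part of the primary endpoint. Patients lost early go the same way, although a Cox analysis can simply censor them.

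In a noninferiority trial the per-protocol analysis is there to show whether deviations have diluted a real difference. A PPS without deaths cannot do this for the most serious component: an excess of cardiovascular death in either arm would not show in it. The Introduction cites a trial on an aspirin background in which ticagrelor lowered cardiovascular death by 21.6% relative to clopidogrel, so this is a component on which the article's own background suggests a difference. The PPS comparison for Step 1 would lose fatal bleeds in the same way.

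**Working it through.** **The plan's own figure.** Section 2.9 gives 655 per arm for an 18.9% event rate, margin 1.38, one-sided 0.025 and 80% power. On the log risk-ratio scale, n = (1.96 + 0.842)² × 2(1 − 0.189)/0.189 ÷ (ln 1.38)² = 649.3, so 650, within 1% of 655. Then 655/0.89 = 736. The PPS wording does not touch the sample size.

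**Inputs for the illustration.** From section 2.9: 18.9% ticagrelor composite, HR margin 1.38, and 736 per arm less 1% lost (736 × 0.99 ≈ 729). From the Introduction: the 21.6% reduction, read as a hazard ratio of 0.784, or 1/0.784 = 1.276 for clopidogrel. Assumed, because the documents give no death rate: ticagrelor cardiovascular death of 3%, 5% or 7%; non-cardiovascular death of 1%; constant, independent hazards; equal hazards between arms for the other components. The PPS is taken as patients alive at 12 months.

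**Step 1: share of the composite hazard due to cardiovascular death.** Total hazard = −ln(1 − 0.189) = 0.2095. Cardiovascular-death hazard = −ln(1 − 0.03), −ln(1 − 0.05), −ln(1 − 0.07) = 0.0305, 0.0513, 0.0726. Shares: 14.5%, 24.5%, 34.6%.

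**Step 2: HR if clopidogrel has a cardiovascular-death HR of 1.276.** Full-analysis HR = 1 + share × 0.276 = 1.04, 1.07, 1.10. In the PPS only the other components remain, and these are equal by assumption, so the HR is 1.00. In simulation (1,500 replicates per case) the PPS met the margin 69%, 64% and 55% of the time, against 65%, 57% and 49% for the full analysis, despite having fewer events.

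**Step 3: events lost if there is no difference.** The full analysis has about 274 events. PPS events = 1458 × (1 − CV death) × 0.99 × (1 − e^(−other hazard)), with other hazard 0.1790, 0.1582, 0.1369.

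| Assumed CV death | PPS events | Events lost | Chance of meeting 1.38, closed form | Simulated |
|---|---|---|---|---|
| Deaths kept | 274 | – | 76% | about 75% |
| 3% | 230 | 16% | 68% | 66% |
| 5% | 201 | 27% | 63% | 62% |
| 7% | 172 | 37% | 56% | 57% |

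Closed form: Φ(√(events/4) × ln 1.38 − 1.96). It agrees with the simulation to within 2–3 points. The starting value is below 80% because this calculation is on the Cox HR scale, whereas the 655 fits a risk-ratio formula; that is a separate matter.

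**Step 4: another route.** With 655 per arm there are 2 × 655 × 0.189 ≈ 248 events and 71.7% power. If patients who die make up 10%, 20%, 30% or 40% of those with a primary event (assumed), 223, 198, 173 or 149 events remain and power is 67.1%, 62.0%, 56.4% or 50.1%.

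The two effects run in opposite directions. Lost events make the margin harder to meet in the PPS. A hidden excess of death on clopidogrel makes it easier.

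**The case against.** Several points on the other side are sound.

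- **The FAS decides.** A reader might infer that noninferiority itself is tested without cardiovascular deaths. It is not: Step 2 is judged primarily on the FAS, which keeps every death. Fatal bleeds likewise stay in the FAS, and the safety set has no completeness condition either. This stands in full and confines the point to the supportive analysis.
- **The alarming case is not a false claim.** If the true composite HR is 1.38 and the whole excess is cardiovascular death, the PPS meets the margin 53–66% of the time. A reader might take that as a large false-positive risk. In the same case the FAS passes only about 2–3% of the time, and both sets pass together about 3%, so nearly all those PPS passes are FAS–PPS disagreement, which the plan does not count as robustness. The case also needs a cardiovascular-death HR of 3.6, 2.6 or 2.1 (1 + 0.38/share), a stress test and not a forecast.
- **The text never says that deaths are removed.** A patient followed to death could be held to have completed every assessment that fell due. Section 2.9 supports that intent: it deducts only loss (1%) and drop-out (10%) to reach 655, and applies the full 18.9%, deaths included, to that number. Removal of all deaths is therefore the literal reading, not an explicit statement.
- **Appendix 5 or an analysis plan may settle it.** Neither is shown. But Appendix 5 is cited for major deviations, and the completeness condition is a further clause. The point concerns a rule that is stated, not a detail left out.

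What remains is that two analysts could build different per-protocol populations from the same sentence, and the literal one selects on outcome.

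**Conclusion.** The point holds for the PPS only. Taken at its word, the condition removes adherent patients who die before month 12, and patients lost early, from a time-to-event analysis that does not need complete follow-up. Agreement between FAS and PPS would then say little about cardiovascular death, although the plan presents that agreement as demonstrating robustness. The decisive FAS test and the sample size are untouched.

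The size rests on the assumed 3–7% cardiovascular death, on equal and independent hazards for the other components, and on the literal reading. Within those limits, the cited 21.6% difference shifts the PPS HR modestly, from 1.04–1.10 to 1.00. With no difference, the PPS loses roughly one-sixth to three-eighths of its primary events and some 10 to 20 points of its chance of meeting the margin. This should be corrected before database lock; it is not a flaw in the primary analysis.

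**What to change.** Either delete the completeness condition from the PPS definition, or state that a patient followed until death or a primary event counts as having completed the efficacy assessments. In both cases add that otherwise eligible and adherent patients with incomplete follow-up stay in the PPS, that their events up to that time count, and that they are censored at last contact. Keeping withdrawn or lost patients is partly a design preference, but it suits the planned Cox analysis and avoids a second selection on post-randomisation behaviour.

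The cost is one sentence before database lock and a slightly less strict PPS. No additional patients or data are needed.

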### Study administration and management

2.10

The local Institutional Review Board or Ethics Committee at each participating co‐center must approve the study, and all patients must provide written informed consent before enrollment. Funding will be provided by the Department of Cardiology, the First Affiliated Hospital of Nanjing Medical University for the co‐centers. The First Affiliated Hospital of Nanjing Medical University will preserve the complete study database and perform all key analyses. The Steering Committee, independent Data Safety Monitoring Board (DSMB), and ERC have been set for the safety control and the evaluation of the primary endpoints (see Supporting Information: Appendix 1). The DSMB may make recommendations to the Steering Committee and study sponsor as a result of its monitoring activities.

## DISCUSSION

3

OPTIMA‐4 trial is the first large‐scale RCT investigating the optimal P2Y_12_ inhibitor in combination with dabigatran for ACS patients with concomitant NVAF undergoing new‐generation DES implantation. This trial will add new evidence on the optimal antithrombotic strategy for the above mentioned patients.

TATT was proposed for ACS patients with concomitant AF after PCI to prevent major adverse cardiovascular events (MACEs) over a decade ago.^25^ Nowadays, the ischemic risk for these patients has been reduced due to the improvement of new‐generation DES and the introduction of advanced antithrombotic agents,^11^, ^26^, ^27^ while the bleeding risk becomes prevailing for these patients under TATT.^28^ As a result, DATT has been recommended as the default strategy for non‐ST‐segament elevation ACS patients requiring chronic OAC, using a NOAC and a single oral antiplatelet agent (preferably clopidogrel) for 12 months (recommendation level: IA) based on large‐scale RCTs.^7^ Anyhow, evidence of the optimal DATT for these patients is limited. Thus, our OPTIMA‐4 trial is designed to compare clopidogrel with ticagrelor in dabigatran‐based DATT for ACS patients with concomitant NVAF and undergoing new‐generation DES implantation, by which we aim to provide evidence for future guidelines in determining the optimal P2Y_12_ inhibitor for these patients.

PLATO trial demonstrated that for ACS patients treated with clopidogrel plus aspirin, the risk of major bleeding not related to coronary‐artery bypass grafting was significantly decreased compared with those treated with ticagrelor plus aspirin.^11^ Thus, it is probable that clopidogrel is superior to ticagrelor in dabigatran‐based DATT with respect to safety. On the other hand, the real‐world evidence showed that in Chinese ACS patients who underwent new‐generation DES implantation, clopidogrel was comparable to ticagrelor in aspirin‐based DAPT in reducing the incidence of MACEs.^29^ Therefore, clopidogrel could be noninferior to ticagrelor in combination with dabigatran concerning the efficacy in ACS patients with concomitant NVAF. In OPTIMA‐4 trial, we presume that for ACS patients with concomitant NVAF and implanted with new‐generation DES, clopidogrel is superior to ticagrelor regarding the safety, and noninferior to the latter regarding the efficacy when coadministered with dabigatran.

To evaluate the benefit‐risk balance, the primary endpoints of OPTIMA‐4 trial contain both safety and efficacy endpoints. The primary safety endpoint is set as major bleeding and CRNMB, which is consistent with the relevant RCTs,^5^, ^8^, ^9^, ^10^ and the primary efficacy endpoint in this trial includes both the cardiocerebrovascular and the peripheral vascular events. The anticipated incidence of major bleeding and CRNMB in each group and noninferiority margin ratio of efficacy endpoint are referred to the RE‐DUAL PCI trial, which contained DATT of dabigatran and a P2Y_12_ inhibitor of either clopidogrel or ticagrelor.^9^

The hierarchical statistical procedure is first based on the hypotheses that the clopidogrel group is superior to the ticagrelor group regarding the safety endpoint, and then noninferior to the latter regarding the efficacy endpoint. This design mainly concerns the major bleeding and CRNMB under DATT, which may result in unexpected discontinuation of antithrombotic agents and consequent increase of the ischemic risk.

The main inclusion and exclusion criteria are set on the basis of the following considerations. First, as only new‐generation DES is required to be implanted in this trial, and the high thrombotic risk scenario such as left main coronary artery DES implantation will be excluded, it would be acceptable to initiate DATT within 5 days after PCI, instead of after 1‐week  1‐month TATT. Second, because all enrolled patients will receive dabigatran‐based DATT, they need to meet the criteria of CHA_2_DS_2_‐VASc score ≥ 2 which indicates high risk of thromboembolism and requirement of anticoagulant. Third, patients with acceptable risk of bleeding (e.g., HAS‐BLED score ≤ 3) will be recruited, whereas those with high risk of bleeding will be excluded, considering the fact that 12‐month DATT has been recommended by current guidelines for the latter.^7^ Besides, previous studies enrolled patients with the average HAS‐BLED score ≤ 3 and showed the superiority of 12‐month NOAC‐based DATT.^5^, ^8^, ^9^, ^10^ Finally, valvular AF patients will not be enrolled owing to little evidence that NOAC is beneficial for these patients.^30^

